**Target Trial Emulation**

| **(A) Research Question** | ***What is the causal effect of exposure to nifedipine on adverse maternal and neonatal outcomes, compared with exposure to labetalol?*** | |
| --- | --- | --- |
|  | **Target Trial (Giant PANDA)** | **Emulation** |
| **(B) Populations** | All women with hypertensive disorders of pregnancy (chronic hypertension, gestational hypertension, or preeclampsia) requiring antihypertensive medication at gestational age 11^+0^-19^+6^; 20^+0^-27^+6^; and 28^+0^-36^+6^.  *Exclusions:* contraindication to labetalol or nifedipine; on both labetalol and nifedipine prior to randomization; unable to provide informed consent; unable to be randomized. | All women with hypertensive disorders of pregnancy (gestational hypertension, chronic hypertension, or preeclampsia) requiring antihypertensive treatment (dispensed labetalol or nifedipine) between 11^+0^ and 36^+6^ weeks’ gestation.  *Exclusions:* Taking both labetalol and nifedipine prior to 11 weeks’ gestation. |
| **(C) Treatment strategies** | Primary  Intention-to-treat (ITT): All women randomized to labetalol or nifedipine, regardless of discontinuation or crossover of treatment groups.    Sensitivity  Per-protocol: All women randomized to labetalol or nifedipine, who continued with assigned treatment until no longer indicated.  On-treatment: All women randomized to labetalol or nifedipine, who continued with assigned treatment until no longer indicated and who self-reported ≥90% adherence across all study contacts. | Primary  Intention-to-treat (ITT): All women who received ≥1 prescription and dispensation of labetalol or nifedipine, including those who received both medications during the study period (crossover will be determined by timing of dispensation) and those who discontinued treatment.  *Crossover defined as receiving both labetalol and nifedipine between 11-36 weeks’ gestation.*  Sensitivity  Per-protocol: All women who received ≥1 prescription and dispensation of labetalol or nifedipine during the study period, but did not receive both medications at any time. |
| **(C) Assignment procedures** | Randomized at diagnosis of hypertension requiring medical intervention (1:1 ratio of nifedipine/labetalol). | “Randomized” (via inverse probability weighting) at point of first dispensation of labetalol or nifedipine during the study period (≥11 weeks’ gestation and ≤36+6 weeks’ gestation). |

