| **(D) Follow-up period** | From 11 weeks’ gestation until 28 days post-birth. | From 11 weeks’ gestation until 28 days post-birth. |
| **(E) Outcomes** | **Primary Maternal**  Severe hypertension (systolic blood pressure ≥160mmHg).  **Primary Neonatal**  Composite of stillbirth, neonatal death (until 28 days post-birth), and NICU admission requiring separation of infant and mother (until 28 days post-birth).  **Secondary Maternal**  *Note: Variables denoted with a * are reported with treatment effect and 95% CI, all others are exploratory only and described with summary statistics*.   - Mean antenatal systolic blood pressure* - New diagnosis of preeclampsia* - Severe maternal morbidity (fullPIERS consensus definition)* - Discontinuation of allocated antihypertensive* - Undesirable effects of allocated antihypertensive* - Maternal death* - Indicated birth (induction of PROM)* - Mean antenatal diastolic blood pressure - Proportion of days with antenatal systolic blood pressure ≥140mmHg - Proportion of days with antenatal diastolic blood pressure ≥90mmHg - Diagnosis of eclampsia - Diagnosis of HELLP syndrome - Placental abruption - Components of severe maternal morbidity - Maternal stroke - Prescription of additional antihypertensive drugs - Prescription of alternative antihypertensive drugs - Time from randomization to first discontinuation of allocated antihypertensive - Total number of antenatal hospital inpatient days - Treatment satisfaction - Beliefs about allocated antihypertensive drug - Adherence to allocated antihypertensive drug - Mode of onset of birth   **Secondary Neonatal**  *Note: Variables denoted with a * are reported with treatment effect and 95% CI, all others are exploratory only and described with summary statistics*.   - Major congenital anomaly (as defined by EURO-CAT)* - Birthweight centile* - Need for treatment for neonatal hypoglycemia* - Neonatal unit admission (separation of baby from mother)* - Mode of birth* - Gestational age at birth* - Fetal loss <24^+0^ weeks’ gestation - Fetal loss ≥24^+0^ weeks’ gestation (stillbirth) - Known early neonatal death (up to 7 days post-birth) - Known late neonatal death (7-28 days post-birth) - Principal recorded indication for neonatal unit admission - Length of stay in neonatal unit (and level of care) - Indication for mode of birth - Preterm birth (<37 completed weeks) - Preterm birth (<32 completed weeks) - Birthweight - Birthweight SGA (<10^th^ centile) - Umbilical arterial pH<7 at birth - Apgar score 5min post-delivery - Need for additional resuscitation at birth - Need for respiratory support - Type of respiratory support needed - Type of treatment for hypoglycemia - Lowest blood glucose measurement within 48 hours post-birth - Intracranial hemorrhage - Neonatal seizures - Necrotizing enterocolitis | **Primary Maternal**  Our primary outcome will be a composite of severe maternal morbidity determined by an expert panel, comprising:   - Maternal mortality (all cause) - Eclampsia - HELLP syndrome - Stroke - Cortical blindness - Retinal detachment - Pulmonary oedema - Placental abruption - Liver rupture - Need for dialysis - Need for extracorporeal membrane oxygenation (ECMO)   *Note: We do not have reliable ascertainment of ICU/HDU admission data. By instead including only severe morbidities which can reasonably be attributed to hypertensive disorders, we will provide a more accurate picture of the effect of disease-modifying drugs.*  **Primary Perinatal**  Our primary perinatal outcome will be a composite outcome determined by expert consensus. This will comprise.   - Stillbirth (fetal death ≥20 weeks’ gestation) - Neonatal death (death within 28 days of birth) - Severe neonatal morbidity, including:   - Bacterial sepsis   - Birthweight < 3^rd^ centile   - Cardiac arrest   - Hypoxic-ischemic encephalopathy (HIE)   - Intracranial hemorrhage   - Necrotizing enterocolitis   - Neonatal asphyxia   - Neonatal seizures   - Requirement for intubation or mechanical ventilation   - Requirement for resuscitation (mechanical or non-mechanical)   *Note: We do not have reliable ascertainment of NICU admission data. Many infants who are born following hypertensive pregnancies will be admitted to NICU without any other severe morbidities. By instead including only diagnosed severe morbidities, we will provide a more accurate picture of the effect of disease-modifying drugs.*  **Secondary Maternal**  *Note: Variables denoted with a * are reported with treatment effect and 95% CI, all others are exploratory only and described with summary statistics*.   - Pregnancy prolongation (time from first antihypertensive dispensation to birth)* - Need for additional antihypertensive(s)* - Individual components of the primary composite outcome - Disease progression (new diagnosis of preeclampsia after randomization)   **Secondary Perinatal**  *Note: Variables denoted with a * are reported with treatment effect and 95% CI, all others are exploratory only and described with summary statistics*. *** Indicates core secondary outcome.*   - Preterm birth (<37; <34; <32; and <28 weeks’ gestation)** - Major congenital anomaly (as defined by EURO-CAT)* - Neonatal hypoglycemia* - Respiratory distress - Neonatal hypothermia - Individual components of primary composite outcome - Birthweight <10^th^ centile |

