| **(F) Causal contrasts of interest** | **Binary Outcomes**  Relative risk (RR) and risk difference (RD) of each outcome (point estimate RR 95% CI) | **Causal comparison:**  *What is the causal effect of exposure to nifedipine during pregnancy on adverse maternal and perinatal outcomes, compared with exposure to labetalol?*  **Estimand = Average treatment effect (ATE)**  Relative risk (RR) and risk difference (RD) of developing each adverse outcome (ATE RR 95% CI).  ***Estimator model*** *–*Doubly robust inverse probability weighting with regression adjustment. |

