**Developing a causal model using directed acyclic graphs (DAGs) to both identify and summarise causal pathways.**

1. Potential confounders will be determined by the above-named authorship team (a quorum of specialists with expert knowledge). All potential confounders are pre-exposure or at exposure.
   1. Covariates to be included in the selection model:
      1. Type of hypertension (gestational hypertension, chronic hypertension, preeclampsia)*
      2. Maternal diabetes mellitus (yes/no)*
      3. Plurality (1/2+)*
      4. Pre-existing renal disease
      5. Pre-existing autoimmune disease
      6. Maternal smoking during pregnancy
      7. Maternal body mass index
      8. IVF/ART conception
      9. Maternal socioeconomic status (SEIFA quintile)
      10. Maternal age at delivery
      11. Mode of birth (neonatal outcomes only)

*Variables denoted with * are included in the Giant PANDA randomization algorithm.*

**Causal pathway and confounding** (excerpt from Causal Inference, What if. M Hernan & J Robins p85: <https://www.hsph.harvard.edu/miguel-hernan/causal-inference-book/>)

*“...the bias has the same structure: it is due to the presence of a cause (known covariate L or unknown covariate U) that is shared by the treatment A and the outcome Y, which results in an open backdoor path between A and Y. We refer to the bias caused by shared causes of treatment and outcome as confounding…”*

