**Define treatment strategy (exposure), assignment procedures, and follow-up period.**

1. The target trial would randomize at the point of diagnosis of a hypertensive disorder of pregnancy (chronic hypertension, gestational hypertension, or preeclampsia). Women would be randomized in a 1:1 ratio to either labetalol or nifedipine. Follow-up would be until 28 days postpartum, and reasons for drop out would include non-adherence to medication, failure to provide consent, unplanned crossover of participants, and random loss to follow up.
2. In the emulated trial, women will be ‘randomized’ at the point of first dispensation of either labetalol or nifedipine at or beyond 11 weeks’ gestation. We will exclude women who were taking both medications prior to 11 weeks’ gestation (unable to be randomized). We will exclude hypertensive women who received neither labetalol or nifedipine (contraindication or non-indication; this cohort will be described). We will also exclude women without hypertension who received labetalol or nifedipine (this cohort will be described).

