3. Total number of dose(s) of allocated antihypertensive drug (mean, SD)
4. In the target trial, there were several **secondary perinatal outcomes** (see *Target Trial Emulation* Table Sfor full list). In our emulation, we will report the following secondary outcomes with treatment effect and 95% confidence intervals (CI):
   1. Preterm birth <37; <34; <32; and <28 weeks’ gestation (yes/no)
   2. Birthweight ≤3^rd^ centile (yes/no)
   3. Neonatal hypoglycemia (yes/no)
   4. Major congenital anomaly as defined by EURO-CAT (yes/no)

Additionally, the following outcomes will also be reported in an exploratory capacity (i.e., with summary statistics only):

1. Individual components of the primary composite outcome (all yes/no)
2. Birthweight <10^th^ centile (yes/no)
3. Mode of birth (spontaneous vaginal, operative vaginal, elective caesarean section, emergency caesarean section)

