**(A) Selection model using inverse probability weights (IPW)**

We will model exposure assignment using inverse probability weighted propensity scores, derived from the logistic exposure model, and including the minimization variables. Adequacy of balance achieved by propensity score weighting will be assessed using: (i) standardized mean difference for model covariates and variance estimates between exposure groups; and (ii) propensity scores overlap, to assess positivity assumption. A finding of lack of positivity will lead to measures such as: addition of interaction terms; different exposure models; use of alternate weighting structures (overlap or stabilized); and lastly, propensity score-based trimming, with the aim of achieving overlap in the propensity score distributions.

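### Birth before 28, 32 and 34 weeks is estimated in all women, including those already past the cut-off at time zero, with no stated adjustment for gestation at first dispensation

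*SAP*

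**What the plan says.** - **Time zero.** The SAP section on treatment strategy, assignment and follow-up says that "women will be ‘randomized’ at the point of first dispensation of either labetalol or nifedipine at or beyond 11 weeks’ gestation". The assignment row of the Target Trial Emulation table bounds this at "≥11 weeks’ gestation and ≤36+6 weeks’ gestation".
- **Outcome.** The outcome definitions list "Preterm birth <37; <34; <32; and <28 weeks’ gestation (yes/no" among the secondary perinatal outcomes that receive a treatment effect and 95% CI. The outcomes row of the emulation table lists "Preterm birth (<37; <34; <32; and <28 weeks’ gestation" with a double asterisk, which its key gives to core secondary outcomes.
- **Effect measure.** The causal-contrast row specifies "Relative risk (RR) and risk difference (RD) of developing each adverse outcome", as an average treatment effect. One study population serves every outcome; no cut-off has its own denominator.
- **Adjustment.** Under "Covariates to be included in the selection model" the SAP names eleven items, and gestation at first dispensation is not one of them. The weighting section derives the weights from a logistic exposure model "and including the minimization variables". The only covariates starred as belonging to the target trial's randomization algorithm are hypertension type, diabetes and plurality. The balance tables of both fitted primary models also lack gestation at start.
- **Where start timing does appear.** It is a row, in three gestational bands by drug, of the (unfilled) descriptive table in Part One. It is also a subgroup factor in Part Three, where no outcomes are named.

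**The concern.** A woman first dispensed at 29 weeks cannot give birth before 28 weeks, and one first dispensed at 35 weeks cannot give birth before 28, 32 or 34 weeks. Both stay in the denominator as non-events fixed at time zero. Gestation at first dispensation therefore strongly determines these three outcomes. If it also differs between labetalol and nifedipine users, it is a confounder, and weights that omit it balance it only so far as it correlates with the covariates that are included.

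The SAP rests its causal reading on conditional exchangeability. For core secondary outcomes reported as causal RRs and RDs, a difference in when the two drugs are started could be read as a difference in what they do. A second, milder consequence is for interpretation: the RDs at the four cut-offs would rest on different, unreported shares of women who could have the event.

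**Working it through.** **No figure to reproduce.** The SAP gives neither preterm birth rates nor the distribution of start timing by drug. Its detectable differences (3.0% and 5.6%) concern the primary outcomes and do not bear on this point. Everything below except the entry window, the cut-offs, the 7,500 women split 90/10 and the balance-table figures is an assumption, made to show the mechanism and its range.

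**Step 1: which cut-offs are affected.** Entry runs from 11+0 to 36+6. Entry after 28+0, 32+0 or 34+0 is allowed, so the <28, <32 and <34 outcomes contain structural non-events. Every woman enters before 37+0, so <37 does not.

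**Step 2: the mechanism.** Let s be the share of a drug group first dispensed before the cut-off and r the risk among them, equal for both drugs (no drug effect). The observed risk is s × r, so

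- spurious RR = s(nifedipine) / s(labetalol);
- if the shares are equal, RR = 1 under no effect, and any true RD among women at risk is multiplied by s.

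With s(labetalol) = 45%:

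| s(nifedipine) | Spurious RR |
|---|---|
| 35% | 0.35/0.45 = 0.78 |
| 40% | 0.40/0.45 = 0.89 |
| 45% | 1.00 |
| 50% | 0.50/0.45 = 1.11 |
| 55% | 0.55/0.45 = 1.22 |

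As a yardstick, the standardised difference for 45% v 35% is 0.10/√[(0.45×0.55 + 0.35×0.65)/2] = 0.21, and for 45% v 55% it is 0.20. A five-point gap gives 0.10. The largest raw values in the SAP's balance tables are 0.1759 (maternal) and 0.1889 (neonatal), both for ART/IVF conception. The ends of the range are thus slightly beyond any raw imbalance that the SAP reports.

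**Step 3: risk that varies with start timing.** Assume that starts at 28 weeks or later split 30/20/50% over 28–31, 32–33 and 34–36 weeks. Assume these risks, identical for both drugs, for starts at 11–19, 20–27, 28–31, 32–33 and 34–36 weeks:

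- <28: 2, 6, 0, 0, 0%
- <32: 5, 12, 12, 0, 0%
- <34: 9, 18, 22, 15, 0%

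Labetalol users start 25/20/55% in the SAP's three bands. Example for <28: labetalol 0.25×0.02 + 0.20×0.06 = 0.0170. Nifedipine at 30/25/45% gives 0.30×0.02 + 0.25×0.06 = 0.0210, so RR 1.24. Nifedipine at 15/15/70% gives 0.0120, so RR 0.71. The true RR is 1.00 throughout.

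| Nifedipine timing | Cut-off | RR, all women | RR, women at risk only |
|---|---|---|---|
| 30/25/45% | <28 | 1.24 | 1.01 |
| | <32 | 1.09 | 0.98 |
| | <34 | 1.04 | 0.97 |
| 15/15/70% | <28 | 0.71 | 1.06 |
| | <32 | 0.90 | 1.09 |
| | <34 | 0.97 | 1.08 |

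The second scenario is a large imbalance: 45% v 30% at risk of birth <28 weeks, a standardised difference of 0.31.

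**Step 4: what the table shows.** The marked distortion is at <28 weeks. Restriction removes most of it there, but at <34 in the second scenario restriction alone moves the RR from 0.97 to 1.08, because timing within the at-risk group still differs. Adjustment for gestation at start is therefore the main remedy. Adjustment without restriction is awkward too: in a logistic model for <28 weeks, a start band from 28 weeks onward has no events and is predicted perfectly.

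**The case against.** The strongest reply is that keeping women past the cut-off is not itself an error. In the declared population the RD is the average treatment effect that the SAP sets out to estimate, and the RR is not diluted. The target-trial column also lists preterm birth <32 weeks with entry up to 36+6. This stands: the denominator alone does not bias the RR. But in that trial randomization balances start timing, and preterm birth there is exploratory, with summary statistics only. The emulation has no such protection and promotes the outcome to effect estimates.

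A reader might go further and infer that the <28, <32 and <34 results will reflect start timing rather than drug effect. The documents do not support that. Bias requires timing to differ by drug after weighting, and the SAP reports no timing by drug. Hypertension subtype and the other weighted covariates may also carry part of any difference.

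Adjustment in the preterm models cannot be wholly excluded either. The DAG figures are not shown, the balance tables cover only the primary models, and the minimization variables are not fully listed. Still, the covariate list and both fitted models point the other way.

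The timing subgroups in Part Three help only in part. The first two bands contain only women first dispensed before 28 weeks, but no outcomes are named, the 32- and 34-week cut-offs are not isolated, and the pooled estimates are unchanged.

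**Conclusion.** The point holds as a gap in specification, not as a demonstrated bias. The plan defines no at-risk set for birth <28, <32 or <34 weeks and leaves gestation at first dispensation out of its stated adjustment set, although the variable is available. These core secondary contrasts are therefore open to confounding by start timing, most strongly at <28 weeks. If timing is balanced between the drugs, the RR is sound and the RD is merely scaled by the share at risk.

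The size cannot be derived from the SAP. Under no drug effect and equal risk among women at risk, assumed shares of 45% v 35% to 55% give a spurious RR of about 0.78 to 1.22. Where risk varies with start timing, the two assumed scenarios give 0.71 and 1.24 at <28 weeks but only 0.97 and 1.04 at <34. The <37 outcome has no structural non-events, and the primary outcomes are not addressed by this point.

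**What to change.** 1. Add gestation at first dispensation to the selection and outcome models for the preterm birth outcomes, and show its balance before and after weighting.
2. Estimate birth <28, <32 and <34 weeks only in women first dispensed before 28+0, 32+0 and 34+0 respectively, with weights re-estimated in each set. Membership is fixed at time zero, so this conditions on nothing that follows treatment. Leave <37 in all women.
3. Report the number at risk by drug for each cut-off.

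**Cost.** SAP wording, plus three outcome-specific weight models, each run through the planned 1,000 × 2 = 2,000 completed data sets. No events are lost, because the excluded women cannot have one. Denominators shrink and the models become sparser. With about 750 nifedipine users and an assumed 45% at risk, the <28 set holds about 337 of them; at the assumed overall risk of 1.7% that is about 750 × 0.017 ≈ 13 events, the same number as without restriction. The adjustment model for <28 weeks must be kept small accordingly. Because the document already reports balance results from the fitted primary models, the change should be dated and declared as made after that stage.

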**Causal contrasts of interest**

1. **Estimand**

**Maternal outcomes** – relative risk (RR) and risk difference (RD) of primary composite outcome and pre-specified (*) secondary outcomes (ATE RR, 95% CI).

**Neonatal outcomes** – relative risk (RR) and risk difference (RD) of primary composite outcome and pre-specified (*) secondary outcomes (ATE RR, 95% CI).

In the Giant PANDA RCT, the primary neonatal binary outcome is estimated using a type of logistic regression (log-binomial) model. We will use a logistic regression model with robust standard errors (to adjust for maternal clustering). This model provides predictive probabilities that are then used to calculate both the between exposure difference (RD) and relative risk (RR) for all binary and highlighted (*) secondary outcomes.

In our emulated target trial, the estimand is the average treatment effect (ATE) between exposures, presented using both RD and RR metrics. Within the potential outcomes framework, a causal interpretation can be made under the assumptions of counterfactual consistency, ignorability (conditional exchangeability), and positivity. Counterfactual consistency means that the definition of exposure is consistent for all individuals. Ignorability states that treatment assignment can be considered exchangeable (i.e. as if the assignment was randomized) after controlling for, or conditioning on, a set of covariates. This implies that there are no important unmeasured confounders, an untestable assertion. The positivity assumption means that, for all observations, the conditional probability of being exposed and of not being exposed (receiving treatment or not receiving treatment) are both greater than zero.

1. **Estimators**

In the emulated target trial, all estimators are targeting the ATE estimand detailed above. Each estimator is specific to the complete process used from the input (observational dataset) to model-based calculation of the ATE. These include: the methods and detailed modelling used in handling missing data; the analysis model used for outcome estimation; compatibility between the imputation and outcome models; and methods used to estimate variance when combining results across imputations and/or bootstrap samples. In the setting of complete data (following multiple imputation) both parametric doubly robust (DR) or non-parametric DR (e.g., machine learning data adaptive) methods, that combine selection and outcome regression models, can provide minimally biased ATE estimates if one of these regression models is correct. Valid 95% confidence limits require that uncertainties in both imputation and outcome models are accounted for (*vide infra*).

